### Sample Size

The sample-size calculation was based on a substudy from the Sheffield ASPIRE registry with 132 patients suspected for CTEPH (12). The prevalence of CTEPH was around 60% here, sensitivities and specificities were 96 and 90% for Q-SPECT and 97 and 92% for functional MRI. It was not appropriate to directly utilize these numbers for sample size estimation: First, the primary analysis of the CHANGE-MRI trial uses different, unconventional endpoints due to the incomplete verification by CPA/CTPA. Second, it was unclear, in how far unverified (by CPA/CTPA) patients will occur in the study setting and how large the resulting differential verification bias might be.

Thus, a simulation study was conducted based on the ASPIRE study simulating 1,000 patients in different scenarios. Estimates for the primary endpoint proportions were taken from the mean diagnostic table of 5,000 simulation runs (see Table 2): the proportions of patients with positive MRI within those with positive SPECT and positive gold standard was estimated to be 98% and the proportion of patients with positive MRI within those with negative SPECT and negative gold standard was estimated to be 6%. These estimates were used for sample size calculations with a Chi^2^-test. For both co-primary hypotheses, a one-sided type-I-error of 2.5% and a power of 80% were used. Sample size calculations for the individual hypothesis resulted in 331 patients with positively verified SPECT and 388 patients with negative SPECT and negative gold standard. To calculate the expected overall sample size to achieve this sample sizes for the subgroups, the expected diagnostic table was calculated based on the simulation study. For each hypothesis, the expected overall sample size was calculated taking into account the expected prevalence of each subgroup (58 and 36%, respectively, see Table 2). Consequently, the final sample size was determined by the higher sample size, which is associated with the second primary objective [Table 2, part (b)]. A total of *N* = 1080 required patients are anticipated.

**Table 2 T2:** Sample size calculation based on a simulation study: **(A)** Expected diagnostic table and **(B)** expected required sample sizes for the co-primary endpoints.

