### Objectives

The diagnostic strategy for CTEPH is basically composed of two components leading to a final diagnosis for or against CTEPH:

Presence of chronic pulmonary embolism, andPresence of elevated pulmonary artery pressure.

The tests to be compared in this study (MRI vs. SPECT) are diagnostic interventions for chronic pulmonary embolism (chronic PE). Diagnosis of elevated pulmonary artery pressure follows the routine clinical assessment with right heart catheterization. As such, the study primarily deals with the first step diagnosis of chronic pulmonary embolism. The medical hypothesis of the CHANGE-MRI trial is that the diagnostic performance of novel functional lung MRI is sufficient to be an equal rights alternative to VQ-SPECT—the current clinical standard—in the detection of chronic PE in the diagnostic algorithm for CTEPH and thus can reduce the radiation burden for patients. Therefore, the MRI should identify almost all correct cases in the SPECT—strategy and should not increase the rate of false positive findings

The study will be considered successful in demonstrating that MRI can replace SPECT if the following co-primary hypotheses can be confirmed for the interrelation of MRI and SPECT:

The probability that MRI is positive in patients who are SPECT positive and who have a positive gold standard is **larger than 95%** and,The probability that MRI is positive in patients who are SPECT negative and who have a negative gold standard is **smaller than 10%**.

To determine the sensitivity and specificity of functional MRI as co-primary endpoints of this diagnostic study, an alternative strategy would have been to send all study patients for a verification step with CPA/CTPA. However, this strategy was considered to imply an unacceptable increase in the diagnostic burden and radiation for patients who are not usually subjected to further diagnostic interventions.

Secondary objectives are:

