#### Diagnostic Gold Standard

Catheter pulmonary angiography or computed tomography pulmonary angiography (CPA/CTPA) is considered to be the current clinical gold standard for confirming chronic pulmonary embolism in a diagnostic algorithm (7). CTPA and CPA are well suited as verification step for the diagnosis of chronic pulmonary embolism (18). Nevertheless, they both have a considerable radiation burden on the patient. Therefore, in current diagnostic practice, in many expert centers only patients with a positive SPECT undergo a verification step with CPA/CTPA, whereas at some sites CPA/CTPA is used for verification of all patients. In this study, we only verify patients, if verification with CPA/CTPA is clinical routine at the respective study site. It is the responsibility of the treating pneumologist to decide whether verification by CPA/CTPA is clinically indicated. In any case, verification with CPA/CTPA is not part of study directives but a clinical decision.

A clinical follow-up after 6–12 months is implemented, where all patients are contacted and asked whether there has been any further intervention indicative (or contraindicative) of CTEPH, in order to identify cases diagnosed as false negative (or false positive, respectively) in the diagnostic work-up. Additionally, cases diagnosed as false negative by the screening test (SPECT negative patients are not verified by CPA/CTPA on a regular basis), but subsequently identified as positive can be captured by incorporation of the clinical follow up. Since the gold standard should capture the true diagnosis at inclusion, the clinical follow up diagnosis is restricted to be within 1 year of the inclusion to ensure that CTEPH—if diagnosed in the clinical follow up—was present at the inclusion already and did not develop afterwards.

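### The 6% planning value behind N = 1080 assumes that almost every chronic PE missed by SPECT is later recognised, so the stated 80% power for co-primary endpoint 2 is conditional on that

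*Protocol article*

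**What the plan says.** The Objectives section sets the second co-primary hypothesis: "The probability that MRI is positive in patients who are SPECT negative and who have a negative gold standard is smaller than 10" per cent. Both co-primary hypotheses must be confirmed for success.

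The Sample Size section starts from a registry substudy of 132 patients with a prevalence of about 60%, in which "sensitivities and specificities were 96 and 90% for Q-SPECT and 97 and 92% for functional MRI". It says these figures could not be used directly, partly because it was unclear how many patients would go unverified and "how large the resulting differential verification bias might be". It gives this as a reason for running a simulation. From the mean simulated table (Table 2A) it takes the planning value: "the proportion of patients with positive MRI within those with negative SPECT and negative gold standard was estimated to be 6" per cent. On error rates it states: "For both co-primary hypotheses, a one-sided type-I-error of 2.5% and a power of 80% were used". The result is "331 patients with positively verified SPECT and 388 patients with negative SPECT and negative gold standard". The second requirement, divided by a subgroup share of 36%, gives the total of 1,080.

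On verification, the Diagnostic Gold Standard section says that "SPECT negative patients are not verified by CPA/CTPA on a regular basis". Where no CPA/CTPA was done at work-up, the gold standard is the clinical diagnosis at 6–12 months. The same section says that some sites verify all patients. The Discussion acknowledges possible differential verification bias and names follow-up as the mitigation.

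**The concern.** The simulation is justified by incomplete verification, yet the table taken from it looks like a table with complete recognition. If so, the 6% describes an endpoint that the trial will measure only if follow-up catches nearly every case that SPECT missed.

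The direction of the error matters. A SPECT-negative patient with chronic PE who is never diagnosed is labelled gold-standard negative. If MRI was positive, a correct MRI result is counted as a false positive. The better MRI is at finding emboli that SPECT misses, the worse endpoint 2 looks, although the secondary objectives list exactly that ability as a benefit to be shown. Because endpoint 2 fixes N and both endpoints must succeed, a failure on endpoint 2 could not be read simply as poor MRI performance.

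**Working it through.** **1. The plan's own figures.** One-sample test of a proportion, normal approximation: n = [1.96·√(p0(1−p0)) + 0.842·√(p1(1−p1))]² / (p1−p0)².
- Endpoint 1 (p0 = 0.95, p1 = 0.98): 330.02, rounded up to 331 (stated 331). 331/0.58 = 570.7 (stated 571).
- Endpoint 2 (p0 = 0.10, p1 = 0.06): 387.96, rounded up to 388 (stated 388). 388/0.36 = 1,077.8 (stated 1,080).

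The calculation reproduces. What remains is whether 6% is the right input.

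**2. Margins of Table 2A against the registry.**

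| Quantity | Table 2A | Registry |
|---|---|---|
| Prevalence | 600/1000 = 60% | about 60% |
| SPECT sensitivity | 576/600 = 96% | 96% |
| SPECT specificity | 360/400 = 90% | 90% |
| MRI sensitivity | (562+20)/600 = 97% | 97% |
| MRI specificity | (29+339)/400 = 92% | 92% |

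Had any SPECT-missed case been relabelled gold-standard negative, the gold-standard-positive total would be below 600 and apparent SPECT sensitivity above 96%. Neither is so. All 24 misses (4% of 600) stand under gold standard positive, 20 of them MRI-positive.

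**3. Effect of unrecognised misses.** Let f be the share of the 24 never recognised, the same for MRI-positive and MRI-negative misses. f is an assumption with a possible range of 0 to 1. Per 1,000 patients:
- expected endpoint 2 = (21 + 20f)/(360 + 24f)
- subgroup size at N = 1080: n = 1.08·(360 + 24f)
- power = exact binomial probability that the upper limit of the two-sided 95% Wilson interval lies below 10%.

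Table 2A shows 21/360 = 5.83%, while the sample size used the rounded 6% (21.6/360). The last column starts from the rounded value.

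| f | Expected endpoint 2 | n | Power (from 21/360) | Power (from 6%) |
|---|---|---|---|---|
| 0 | 21/360 = 5.8% | 389 | 85% | 81% |
| 0.05 | 22/361.2 = 6.1% | 390 | 79% | 75% |
| 0.10 | 23/362.4 = 6.3% | 391 | 72% | 67% |
| 0.25 | 26/366 = 7.1% | 395 | 47% | 42% |
| 0.50 | 31/372 = 8.3% | 402 | 18% | 16% |
| 1 | 41/384 = 10.7% | 415 | <1% | <1% |

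**4. Where the expected value passes 10%.** Solve 21 + 20f = 0.10·(360 + 24f): f = 15/17.6 = 0.85. From 21.6: f = 14.4/17.6 = 0.82.

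**5. If SPECT misses fewer cases.** Table 2A implies a SPECT negative predictive value of 360/384 = 93.75%. If it were 99% (assumption), misses would number 360/0.99 − 360 = 3.6 per 1,000. With the same MRI-positive fraction (20/24) and none recognised, endpoint 2 = (21 + 3.03)/363.6 = 6.6%, with power about 63%.

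Endpoint 1 is conditional on SPECT positive and gold standard positive, so this mechanism does not touch it.

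**The case against.** The strongest reply is that f is undocumented and that several features of the design keep it low.
- All patients are contacted at 6–12 months, and that diagnosis overrules CPA/CTPA.
- Some sites verify everyone, and elsewhere the treating pneumologist may order CPA/CTPA. The article blinds the image readers to each other but does not say that the pneumologist is blinded to MRI, so MRI-positive misses may be verified more often than others.
- Verification follows the clinical work-up, hence the in-place SPECT read, whereas the primary endpoint uses the blinded read. Some blinded-read misses will have been in-place positive and verified.
- The Introduction credits SPECT with a negative predictive value of virtually 100%, far above what Table 2A implies.
- The limitation is disclosed, other scenarios were simulated but are not shown, and the registry's reference standard is not described, so its figures may themselves reflect incomplete verification.

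Much of this stands. A reader might infer that the trial will not have 80% power, or that endpoint 2 is expected to breach its 10% limit. The documents support neither. The first depends on an f they do not give, and the second needs about 82–85% of misses to stay unrecognised, which the points above make an extreme case. Nor does the bias create a false success on endpoint 2, since it runs against MRI.

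The reply does not rescue the single figure. Disclosing the bias does not put it into the planning value, and the unshown scenarios were not the table that fixed N. Low f is not enough either: power is already 75–79% at f = 0.05. A higher SPECT predictive value shrinks the effect but still leaves about 63% in the case worked above.

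**Conclusion.** The concern holds in conditional form. The 6% that fixes N = 1080 corresponds to essentially complete recognition of SPECT-missed chronic PE, in a trial that does not routinely verify SPECT-negative patients and that names the resulting bias as a reason for simulating. The stated 80% is met only if recognition is nearly complete. It falls to about 67–72% if one miss in ten goes unrecognised, to 42–47% at one in four and to 16–18% at one in two. These figures rest on Table 2A's 24 misses per 1,000, on 20 of 24 being MRI-positive, and on one f for MRI-positive and MRI-negative misses. Fewer misses, or preferential verification of MRI-positive patients, would reduce the loss. This is a fault in a planning assumption and in how a failed endpoint 2 could be interpreted; the sample-size arithmetic is sound.

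**What to change.** 1. In the Sample Size section, say that the 6% and the 80% power assume near-complete recognition of SPECT misses. Give the planning value and power for endpoint 2 as a range over f, as in the table above.
2. Prespecify a supporting analysis that reports SPECT-negative, MRI-positive patients without CPA/CTPA separately, with two bounds for endpoint 2: all of them counted as MRI false positives, and all counted as true positives and so removed from the gold-standard-negative group.
3. Where numbers allow, also report endpoint 2 in the sites that verify all patients, selected by site policy and not by individual patient. The article does not say how many such sites there are, so this may be imprecise and should serve interpretation only.

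The cost is wording plus analyses of data already being collected. No additional CPA/CTPA, radiation or enrolment is required. The downside is a less favourable stated power.

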**(A) Expected diagnostic table**						
		**Gold standard**				
		**+**		**–**		
		**SPECT**		**SPECT**		
		**+**	**–**	**+**	**–**	
MRI	+	562 (98%)^*^	20 (82%)^*^	11 (28%)^*^	21 (6%)^*^	
	–	14 (2%)^*^	4 (18%)^*^	29 (72%)^*^	339 (94%)^*^	
**Sum**		576 (58%)^#^	24 (2%)^#^	40 (4%)^#^	360 (36%)^#^	1000
**(B) Expected required sample sizes for co-primary endpoints**						
(1) Proportion of patients with MRI+ if gold standard+ and SPECT+		Expected: 98%	Targeted: Min 95%	Required patients gold standard+ and SPECT+: 331	Expected total number required: 571	
(2) Proportion of patients with MRI+ if gold standard– and SPECT–		Expected: 6%	Targeted: Max 10%	Required patients gold standard– and SPECT–: 388	Expected total number required: 1080	

* *Column percentages*.

# *Row percentages*.

### Statistical Analysis

The primary analysis will be performed in a modified intention-to-treat population, i.e., patients will only be excluded from the analysis, if for all three diagnostic tests no assessment (neither in-place nor blinded) is available and no further follow-up data on the clinical diagnosis after 6–12 months is available. The overall two-sided type-I-error probability is set to 5%. Point estimates and 95% Wilson confidence intervals will be calculated for both co-primary endpoints based on the blinded reader assessments. Since both endpoints are evaluated co-primarily, no correction for the overall type-I-error probability is necessary.

Imputation of missing values is conducted dependent on whether any assessments of SPECT, MRI or CPA/CTPA images and clinical follow up diagnosis are available or not. If either in-place or blinded reader assessments are available, missing values of MRI or SPECT will preferably be replaced by the results of the respective available assessments. In the case of missing values because the test has not been performed at all or neither in-place nor blinded assessment are available, missing values of MRI or SPECT will be replaced using a conservative strategy in favor of SPECT, where missing information for the experimental functional MRI in all instances is counted such that sensitivity and specificity are diminished as compared with SPECT.

If missing values occur for all three diagnostics MRI, VQ-SPECT, and gold standard (e.g., because the patient decided against the study directly after written informed consent) and no further follow-up information is available for the patient, the patient is omitted from the analysis population and no imputation will be performed.

Secondary analyses will be performed in line with primary analyses using point estimates and 95% Wilson confidence intervals for the various proportions of interest. Safety endpoints will be evaluated descriptively with absolute and relative frequencies of complications and malfunctions of MRI and SPECT and will be compared using risk differences and the Chi^2^-tests. As sensitivity analyses, the primary analysis will be repeated in the per-protocol population based on the blinded reader assessment, comprising all patients without missing co-primary endpoints. Additionally, a sensitivity analysis will be conducted in the per-protocol population based on the in-place assessment, comprising all patients, where in-place MRI diagnosis has been entered into the eCRF before SPECT assessment so that the blinding can be considered to be intact.

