### The Need for a Trial

VQ-SPECT requires ionizing radiation, while MRI systems are not associated with any additional radiation dose and have increasing availability. Initially, a multicenter study conducted between 2006 and 2008 in 371 patients with suspected pulmonary embolism using Gadolinium-enhanced MR Angiography to detect pulmonary embolism showed a moderate test performance and modest patient compliance [PIOPED III (10)]. Meanwhile, novel 4D dynamic contrast-enhanced (DCE) lung perfusion magnetic resonance imaging (MRI) techniques (11) are widely available on current MRI systems and have shown excellent test performance in diagnosing CTEPH in a single center registry setting in Sheffield [ASPIRE registry (12)]. In addition, a non-contrast, free breathing ventilation perfusion MRI technique, known as the Fourier decomposition MRI method (13), has recently shown initial encouraging results in diagnosing chronic pulmonary embolism (14). In the CHANGE-MRI study we implemented phase-resolved functional lung (PREFUL) MRI as a secondary outcome parameter, which is a further development of Fourier Decomposition MRI depicting the whole breathing and cardiac cycle (15). These novel functional MRI techniques hold significant potential to be an equal rights non-ionizing alternative to VQ-SPECT in the near future, if they can demonstrate robust test performance in a prospective multicenter setting (Figure 2).

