### Outcome Measures

SPECT and MRI will be compared based on a standardized blinded reader assessment of the imaging methods as well as based on the in-place assessments as part of a workflow incorporated into the clinical routine. To definitely exclude information carry-over in the primary analysis, the following co-primary endpoints are calculated based on the standardized blinded reader assessment:

- The proportion of patients with positive MRI in the group of patients who have a positive SPECT diagnosis for chronic pulmonary embolism and who are positive in the gold standard- The proportion of patients with positive MRI in the group of patients with negative SPECT who are negative in the gold standard.

The co-primary endpoint will also be analyzed based on the in-place assessment and results will be compared to assess the inter-rater agreement and context sensitivity of the diagnostic evaluations and to evaluate the external validity and generalizability of the primary results. Additional secondary endpoints based on the in-place assessment and the blinded-reader assessment include the diagnostic measures sensitivity, specificity, positive and negative predictive values of MRI and SPECT as compared to the defined gold standard. To assess additional benefit of the MRI compared to the SPECT, the proportion of patients with positive MRI in the group of patients who have a negative SPECT, but are positive in the gold standard, and the proportion of patients with negative MRI in patients who are SPECT positive, but have a negative gold standard, will be evaluated.

To assess the safety, the occurrence of allergic reactions or other adverse events, non-completed procedures, reasons for non-completion, non-diagnostic procedures, reasons for non-diagnostic, and the quality of the images will be evaluated for both imaging techniques.

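### N = 1080 is planned on complete MRI reads, but the primary analysis counts an MRI with no usable read as an MRI error, so the stated 80% power per hypothesis depends on no MRI being missing

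*Protocol article*

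**What the plan says.** **Imputation rule (Protocol article, Statistical Analysis).** The primary population is modified intention-to-treat. A patient leaves it only if MRI, SPECT and the gold standard are all missing and there is no follow-up information, so a missing MRI alone does not exclude anyone. If one of the two MRI reads exists, it replaces the other. If the MRI was not done, or has neither read, the imputation goes against MRI: "missing information for the experimental functional MRI in all instances is counted such that sensitivity and specificity are diminished as compared with SPECT". In the co-primary endpoints, such a patient counts as MRI-negative among SPECT-positive, gold-standard-positive patients (endpoint 1). Among SPECT-negative, gold-standard-negative patients (endpoint 2), the patient counts as MRI-positive.

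**Sample size (Sample Size and Table 2).** The planning rates are 98% against a 95% minimum and 6% against a 10% maximum, taken from a simulation based on a registry substudy. "For both co-primary hypotheses, a one-sided type-I-error of 2.5% and a power of 80% were used". This gives 331 and 388 patients in the two subgroups. Dividing by subgroup shares of 58% and 36% gives totals of 571 and 1080, and the larger is taken.

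**Related provisions.** Outcome Measures plans to report "non-completed procedures, reasons for non-completion, non-diagnostic procedures" for both techniques. The end of Statistical Analysis plans a repeat of the primary analysis in patients without missing co-primary endpoints. Table 1 excludes patients known to be unable to undergo MRI.

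**The concern.** The two parts of the plan describe different quantities. The sample size treats 98% and 6% as the rates that the primary analysis will see. Under the imputation rule, the primary analysis sees those rates only when no MRI lacks a usable read. Each MRI without a read adds a certain error in a design with only 3 and 4 percentage points between planning value and limit.

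Enlarging N by a dropout factor would not repair this, because these patients stay in the denominator and move the rate itself. At stake is whether the 80% describes the analysis that will be run, and whether the trial could miss its primary criterion although every MRI that was read performed as planned.

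**Working it through.** **Inputs from the document:** one-sided type I error 2.5%; power 80% per hypothesis; 0.98 vs 0.95; 0.06 vs 0.10; subgroup shares 576/1000 and 360/1000; N = 1080; decision by 95% Wilson interval. **Assumption:** a share m of patients has no usable MRI read, equal in both subgroups and unrelated to what the MRI would have shown. The document gives no value for m.

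**1. Reproduce the plan's figure.** One-sample formula: n = (1.960·√(p0(1−p0)) + 0.842·√(p1(1−p1)))² / (p1−p0)².
- Endpoint 1: (1.960·0.2179 + 0.842·0.1400)² / 0.03² = 330.02, so 331. 331/0.58 = 571.
- Endpoint 2: (1.960·0.3000 + 0.842·0.2375)² / 0.04² = 387.96, so 388. 388/0.36 = 1078, stated as 1080.

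The sample-size arithmetic is right, and nothing is left over as an allowance for missing MRI.

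**2. Do the 98% and 6% already contain missing MRIs?** Table 2A classifies all 1000 simulated patients as MRI-positive or MRI-negative. Its margins return the source accuracies exactly. For MRI they are (562+20)/600 = 97% and (29+339)/400 = 92%. For SPECT they are 576/600 = 96% and 360/400 = 90%. No missing-as-error component has been added.

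**3. Rates under the plan's rule.** Endpoint 1: p1 = 0.98(1−m). Endpoint 2: p2 = 0.06(1−m) + m. The limits are reached at m = 1 − 0.95/0.98 = 3.1% and m = 0.04/0.94 = 4.3%. Beyond these values no sample size is sufficient.

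**4. Power at N = 1080.** The expected subgroup sizes are 1080·0.576 = 622 and, as required by the plan, 388. The Wilson rule needs at least 602 MRI-positives of 622 (at most 20 negatives; 0.02·622 = 12.4 expected) and at most 27 MRI-positives of 388 (0.06·388 = 23.3 expected). Exact binomial power follows; the joint figure is the product, since the subgroups do not overlap.

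| m | p1 | p2 | Endpoint 1 | Endpoint 2 | Joint |
|---|---|---|---|---|---|
| 0 | 98.0% | 6.0% | 98% | 82% | 81% |
| 0.5% | 97.5% | 6.5% | 90% | 70% | 63% |
| 1% | 97.0% | 6.9% | 69% | 56% | 38% |
| 2% | 96.0% | 7.9% | 20% | 29% | 6% |
| 3% | 95.1% | 8.8% | 2% | 11% | <1% |

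The approximate formula gives the same picture (for m = 1%: 67%, 52%, joint 35%). Endpoint 2, which sets N, has almost no reserve. Endpoint 1 has some, because 622 exceeds the 331 required; it still has 90% at m = 0.5% but falls below 80% by m = 1%.

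**5. In patients.** An m of 1% is about 4 of 388 and 6 of 622. Four missing MRIs in the endpoint 2 group add 4·0.94 = 3.8 expected errors to the 23.3, which brings the expectation to the cut-off of 27.

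**The case against.** **The rule is narrower than it may sound.** A reader might infer that every missing blinded MRI read counts as an error. The document does not say so: the in-place read is used first, and only an MRI with no read at all is scored against MRI. The relevant m is therefore smaller than the share of missing blinded reads. The article is not explicit about an MRI that was performed but is non-diagnostic; treating it as missing would raise m.

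**The missing rate is unknown.** A reader might infer that the trial is underpowered, or would fail with ordinary non-completion. The documents do not support either. Known inability to undergo MRI is an exclusion criterion, which removes major causes beforehand. The remark that a 2006–2008 MR angiography study "showed a moderate test performance and modest patient compliance" concerns a different technique, which the article contrasts with the present one, so it says nothing about m here. Listing non-completion as an outcome shows that it will be recorded, not how often it occurs.

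**The stated 80% is per hypothesis.** The joint figures are useful for planning but contradict nothing that the document claims.

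**A failure could be explained.** A reader might infer that failure would necessarily be taken for poor accuracy. The planned complete-case analysis and the recorded reasons for non-completion allow the two to be separated, although they do not change the formal primary decision.

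**The rule is deliberately conservative.** It guards against a false claim that MRI can replace SPECT; its price is power, not validity. Relaxing it according to the reason for the missing scan would need judgement and would favour MRI in a trial recruiting since 2016.

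**The article is condensed.** It mentions simulation scenarios that are not shown, and an assumption on missing MRI could lie in the full protocol. But the article gives the whole derivation of N, and it closes without one.

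These points limit the wording and the remedy. They leave the mismatch between imputation rule and planning rates in place.

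**Conclusion.** The point holds as a planning inconsistency whose size depends on m. The sample-size arithmetic reproduces and the conservative rule is legitimate, but the 98% and 6% are not the rates that this rule delivers once any MRI lacks a usable read. The design is sensitive even to small m: at 1%, power falls to 69% and 56% for the two endpoints (38% jointly), and at 2% to 20% and 29% (6% jointly). These figures assume equal m in both subgroups, independence from the true MRI result, planning rates that hold exactly for MRIs that were read, and subgroup sizes as expected. The error direction is conservative: it endangers a true success and does not raise the chance of a false one. The point should be corrected, but it does not undermine the validity of the primary analysis.

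**What to change.** Keep the conservative rule as primary. Restate the power for each endpoint and for joint success under that rule at m = 0, 0.5, 1, 2 and 3%, and say plainly that the 80% per hypothesis applies only with complete MRI reads. In the results, set the already planned analysis of patients without missing co-primary endpoints, and the number of and reasons for non-completed MRIs in each co-primary subgroup, directly beside the primary result. A failure caused by missing MRIs can then be told apart from one caused by misreading.

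This needs a short addition to the sample-size text and a reporting commitment; the plan already collects the reasons for non-completion. The cost is a less favourable stated power. Raising N is not a realistic substitute: by the plan's own formula, endpoint 2 alone would need about 687/0.36 = 1908 patients at m = 1% and 1477/0.36 = 4103 at m = 2%.
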